### Setting

The study will be conducted in two settings of Kenya that have contrasting epidemiological and programmatic characteristics: Kwale County on the south Kenyan coast and Bungoma County in western Kenya (figure 2). Key epidemiological and sociodemographic characteristics of the two study areas are summarised in table 1. Historically, STH infections have been highly prevalent in both regions but recent control efforts have reduced levels of infection. *A. lumbricoides* is more common in western Kenya, whereas hookworm predominates on the coast.^20^
*T. trichiura* is present in both settings, but at low levels. In Kwale County, in addition to STHs, there is focal transmission of *Schistosoma haemotobium*, and LF is endemic.^24–26^ In relation to sociodemographic characteristics, Kwale County is among the poorest in Kenya, with low levels of access to water and sanitation, and minimal primary school enrolment, while Bungoma lies close to national averages for these factors.

**Table 1 BMJOPEN2015008950TB1:** Epidemiological and socioeconomic characteristics in the two study areas

	Bungoma	Kwale County	National average	Source
Helminth infections				
STHs combined (%)	49.3	33.6	32.4*	27
Hookworm (%)	44.3	27.7	15.6*	27
* Ascaris lumbricoides* (%)	28.2	0.8	18.0*	27
* Trichuris trichiura* (%)	0.8	8.9	6.6*	27
* Schistosoma haematobium (%)*	non-endemic	17.5	14.8*	27
* Wuchereria bancrofti* (%)	non-endemic	endemic	endemic in 6 of 47 counties	28
Socioeconomic conditions				
Poverty rate (%)†	52.2	72.9	46.6	29
Access to water and sanitation				
Improved drinking water (%)	72.1	51.2	55.1	30
Improved sanitation (%)	71.2	34.4	64.9	30
School system				
Primary school attendance (%)‡	94.6	87.2	85.6	30
Literacy rate (%)	60.5	66.5	66.4	31
Health system				
Full immunisation coverage (%)§	84.4	77.5	83.0	32
Doctors (per 100 000 people)	4	1	7	32
Nurses (per 100 000 people)	37	37	49	32

*Among schools included in the monitoring and evaluation of the national school-based deworming programme.

†Percentage of population living below the Kenya poverty line (Ksh 1562 per person per month in rural areas and Ksh 2913 in urban areas).

‡Percentage of the official primary school-age population that attends primary school.

§Percentage of population that completed 3+ doses of diphtheria, pertussis and tetanus vaccination.

STH, soil-transmitted helminth.

**Figure 2 BMJOPEN2015008950F2:**
[figure not shown]
Map showing location of study sites and community units.

### Sensitisation and recruitment

Key stakeholders and policymakers have been involved in the study and its design from conceptualisation. Meetings have been held with the MoH and MoEST in Nairobi, and at each study site, where key stakeholders were sensitised about the study objectives, intervention and evaluation procedures, and requested to provide input. Community meetings were held to describe the purpose of the study, the interventions, the evaluation procedures to be followed, and the risks and benefits of participation. Individuals had the opportunity to ask questions. Consent for the intervention was provided at the community level with the option for individuals to opt-out either from receiving treatment or study assessments.

Consent for the baseline and follow-up cross-sectional surveys is obtained at the individual level. Field staff enumerate all households through coordination with the chiefs and village elders. Subsequently, households selected for inclusion into the study are visited by field staff. In each household visited, written informed consent to conduct the household-level questionnaire is sought from the household head. Following this, a random function programmed in a smartphone selects the individual within the household who will provide a stool sample and answer further individual-level questions. Individual-level informed consent is sought from selected individuals (either for themselves or their children) and written assent sought from children over 13 years of age. Inclusion criteria for the selection of individuals include: (1) resident for at least 12 months, (2) willingness of adult aged 18 years and above or parent/guardian to provide written informed consent, and (3) provision of written assent to participate from children aged between 13 and 17 years. Exclusion criteria include: (1) recent (<12 months) resident or visitor to household at time of household visit, (2) refusal of informed consent and (3) refusal to assent by children aged 13–17 years.

### Outcomes

The primary outcome is the prevalence of hookworm (*Necator americanus* or *Ancylostoma duodenale*) infection among all sampled individuals during 30 months of follow-up. Owing to ethical considerations of treating those found infected during surveys, new populations of individuals will be selected for each cross-sectional survey (baseline, 12, 24 and 30 months). All participants are asked to provide a stool sample, which is examined in duplicate using the Kato-Katz method. Individuals found infected are revisited by the study team and treated with albendazole. In a random subset of individuals, additional confirmatory diagnosis of infection is based on real-time PCR, which also allows the differentiation between hookworm spp.^33^
^34^

The main secondary outcomes include:
Prevalence of *A. lumbricoides* and *T. trichiura*, based on expert microscopy and, in a random subsample, on real-time PCR.Intensity of infection for each STH spp, based on quantitative egg counts.Treatment coverage, measured using both routine data, and data collected during household visits to track treatment coverage and compliance.

### Survey procedures

At each house visited, household heads are interviewed to collect a household census and information on household characteristics and ownership of key assets during household visits. Data on household water, sanitation and hygiene (WASH) conditions and school WASH conditions are collected using structured observations and questionnaires, employing tools piloted and extensively used in Kenya.^35^
^36^

Teachers and CHVs will be provided with treatment registers and asked to provide a full record of all individuals who have received treatment. To augment these data, population-based coverage surveys using multistage clustering sampling^37^ will be carried out among a random subsample of communities.

In each cross-sectional survey, a randomly individual selected is asked to provide a stool sample, which is transported to a nearby health facility laboratory and examined in duplicate within 1 h of processing using the Kato-Katz method. Duplicate slides are read by independent microscopists. A 10% quality control check is performed by a supervisor. Aliquots of randomly selected stool samples are preserved in ethanol for confirmatory real-time PCR diagnosis.^33^
^34^ In addition, stool samples will be stored for future molecular analysis, including the detection of potential drug resistance alleles,^35^
^38^ and genome sequence analysis to investigate the genetic structure of helminth populations.^39^

All members of the study teams have been appropriately trained in the study objectives and procedures. Standard operating procedures have been developed, field-tested and revised, and are used to guide all field activities. Supervisors make regular visits to the field to monitor fieldwork.

### Longitudinal studies

In six CUs (one with a medium (20–49%) and one high (>50%) prevalence of hookworm in each study group), individuals will be followed longitudinally to help quantify the transmission dynamics of the parasites and re-parameterise mathematical models of transmission dynamics. An age-stratified random sample of 200 individuals will be chosen and asked to provide complete stool samples for a period of 5 days immediately following treatment. The collected stool will be transported to an off-site sorting facility, *A. lumbricoides* and hookworm will be manually separated from the stool, and the number and sex or worms recorded for each individual. The proportion of unfertilised eggs will also be determined for *A. lumbricoides*, given the importance of this measure as a determinant of how effective a given treatment programme is in driving transmission to extinction by crossing the transmission threshold where insufficient mating occurs to sustain transmission.^40^ Selected individuals will be revisited at 1, 3, 6, 9 and 12 months post-treatment and asked to provide a stool sample, which will be examined for the presence of STH eggs in duplicate using the Kato-Katz method.

We will also conduct household visits to assess the extent of non-compliance to treatment and factors associated with non-compliance.^37^ Adverse events will be monitored in these cohorts during household visits. Reports of severe adverse events that are classified as at least possibility related to the study drugs will be reported to the ethics committee.

### Sample size calculation

Sample size calculations are based on the principles of cluster randomised trials.^41^ Analysis of survey data collected as part of the ongoing monitoring and evaluation of the NSBDP suggests that the prevalence of hookworm, the primary outcome, varies between 5% and 10%, with an intracluster correlation coefficient (ICC) of 0.125.^2^ The assumed difference between the study groups in the prevalence of hookworm after 30 months is based on mathematical modelling of the predicted impact of different treatment strategies,^11^
^12^ and is presented in figure 3 for different degrees of prevalence of infection at baseline. The figure also presents the number of clusters required to detect the smallest predicted difference between school-based treatment and two other arms with 80% power a 5% level of significance, an ICC of 0.125 and 225 participants per cluster. Based on these calculations and taking into account potential loss to follow-up of CUs (assumed to be 5%), a conservative sample size of 40 clusters per group will be used in both study areas.

**Figure 3 BMJOPEN2015008950F3:**
[figure not shown]
The relationship between baseline prevalence of hookworm infection (proportion of all community members found to be infected) and predicted impact following 2 years of treatment for each proposed treatment strategy. Based on a mathematical model of transmission dynamics, assuming 80% treatment coverage of school-based deworming and 70% of community-based treatment. Biannual school-based treatment did not differ significantly from annual school-based treatment and therefore is not shown. Sensitivity of diagnosis is assumed to be 63%.

### Data management

Data are collected in the field using Samsung GT7552 smartphones running android operating system V.4.2. The questionnaires are programmed using Survey CTO software (http://www.surveycto.com) and data are downloaded daily using secure Wi-Fi in the field office into a web-based database. Backup of the database to a central server is performed daily. Laboratory results are recorded in laboratory books by technicians and double-entered into a customised database and saved on a centralised server.

### Data analysis

Primary analysis will be carried out on groups as randomised (intention-to-treat). Results will be presented as appropriate effects sizes with a measure of precision (95% CIs). Clustering by CU will be included in all analyses. Our main analysis of the primary outcome, the prevalence of hookworm, and other secondary outcomes, will be based on cross-sectional analyses comparing the outcome at 30 months follow-up between study groups. Unadjusted and adjusted results will be presented for all analyses. Covariates in adjusted analyses will be specified a priori and will include subcounty and urban/rural classification, household socioeconomic status, and access to adequate water and sanitation. For continuous outcomes, analyses will adjust for baseline by inclusion of the cluster mean of the outcome in question as a covariate in statistical models. For binary outcomes (notably the primary outcome), no baseline adjustment will be made because of issues relating to the non-collapsibility of ORs.

Demographic and other baseline characteristics of clusters will be compared to check for imbalances between study groups. Tabulation of these measures will be generated using the intention to treat data sets. No significance tests will be performed to investigate for differences between groups at baseline. Where imbalances are suspected, further exploratory adjusted analyses will be carried out that include additional adjustment for these factors. Formal statistical testing will be restricted to comparison between the two community-based treatment groups and the school-based treatment group (control). A small number of secondary outcomes will be prespecified for statistical testing along with the primary outcome. No formal adjustment will be made for multiple testing but the number of outcomes formally tested will be restricted to fewer than 10 and the results interpreted with due caution. This includes multiplicity associated with the two experimental arms. No formal comparisons will be made between the two experimental arms as the study has not been powered for this analysis.

A small number of secondary subgroup analyses will be specified in advance and will be carried out using formal statistical tests for interactions. These will include household poverty, remote households, frequent non-compliers of treatment, non-enrolled children, and households without access to adequate water and sanitation. These analyses will help understand the impact heterogeneity of the interventions.

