### Overall study design

Two paired community cluster randomised trials in different settings in Kenya will evaluate the impact and cost-effectiveness of annual school-based deworming, annual community-based deworming and biannual community-based deworming. The trials are designed as cluster randomised, open-label trials with three study groups. The primary outcome is the prevalence of hookworm. This outcome was selected because it is the STH spp that contributes most to morbidity, is responsible for the most DALYs lost due to STH^3^ and is the species most difficult to control using school-based deworming alone.^9^ Allocation to study group is by cluster, using predefined units used in public health provision—termed community units (CUs). The three study groups are:
*Control group*: Annual school-based deworming. Preschool and school children (typically aged 2–14 years) will receive a single dose of albendazole (400 mg) from trained school teachers, as part of the ongoing national school-based deworming programme.*Expanded age range group*: Standard school-based deworming supplemented by annual community-based deworming (2–99 years). All household members who are not enrolled in school will receive a single dose of albendazole (400 mg) from trained CHWs—known in Kenya as community health volunteers (CHVs).*Expanded age range and frequency group*: Annual school-based deworming supplemented by community-based deworming (2–99 years), followed by an additional community-based deworming 6 months later. All household members who are not enrolled in school will receive a single dose of albendazole (400 mg) from trained CHVs.

Mathematical models suggest that there is little difference in the impact of annual or biannual school-based deworming, given the expected prevalence in our study sites,^10^
^18^ and therefore we did not include biannual school-based deworming as a study group. In other settings where *A. lumbricoides* is more common and hookworm is absent, biannual treatment may be desirable due to the relatively higher levels of infection in school-age children compared to adults.

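### Frequent non-compliance is listed for formal interaction tests, but it arises after randomisation and has no control-arm counterpart among adults

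*Protocol article*

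**What the plan says.** The Data analysis section announces a small number of prespecified secondary subgroup analyses that "will be carried out using formal statistical tests for interactions". The listed factors are: "These will include household poverty, remote households, frequent non-compliers of treatment, non-enrolled children, and households without access to adequate water and sanitation". The same section confines formal testing to each community-based arm against the school-based control, so any such interaction needs the subgroup to exist in control.

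Overall study design sets out who is offered treatment:

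- Control: "Preschool and school children (typically aged 2–14 years) will receive a single dose of albendazole (400 mg) from trained school teachers", once a year.
- Both community arms: the school programme, plus community health volunteers for the rest of the household. For the more intensive arm the text reads "All household members who are not enrolled in school will receive a single dose of albendazole (400 mg) from trained CHVs".
- The more intensive arm only: the first round is "followed by an additional community-based deworming 6 months later".

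Under Outcomes, the primary outcome is hookworm "infection among all sampled individuals during 30 months of follow-up", so adults are counted in every arm. Coverage is measured from routine data and from "data collected during household visits to track treatment coverage and compliance". For the surveys, "new populations of individuals will be selected for each cross-sectional survey". The document describes no measure of compliance taken before randomisation.

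**The concern.** An interaction test by subgroup compares the arm effect across strata. It keeps the protection of randomisation when stratum membership is fixed before allocation, or at least cannot be affected by it. Compliance with the trial's own treatment rounds does not meet that condition. Whether someone becomes a frequent non-complier depends on whether they are offered drug, by whom and how often, and this is what the arms vary.

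For adults the difficulty goes further. A control adult is scheduled no treatment and so can neither take it nor decline it. The analyst must code these adults as non-compliers, code them as compliers, or leave them out. Each choice sets a self-selected group in the community arm against a differently composed group in control.

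At stake is the reading of one secondary result. The section says these analyses will help explain impact heterogeneity, and it plans no formal adjustment for multiplicity. A difference produced by the coding could be reported as prespecified, formally tested evidence that the intervention works differently in non-compliers.

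**Working it through.** The plan gives no figure for this analysis, so there is none to reproduce. The check asks what the interaction odds ratio (OR) would be in expectation if neither intervention changed anyone's infection status. The true value is then 1.00.

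**Inputs from the document.** The caption of Figure 3 assumes 80% coverage for school-based and 70% for community-based treatment. These figures are borrowed here as 20% non-compliance in children (both arms) and 30% in adults (community arm). A coverage shortfall is not the same as frequent non-compliance, so this is itself an approximation.

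**Assumptions not in the document.** Children are 40% to 50% of the sample. Hookworm prevalence is 10% in adults and 5% or 10% in children. The odds of infection in reluctant people are 1, 1.5 or 2 times those in willing people.

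**Formulas.** Prevalence in a stratum = sum of (share × prevalence) / sum of shares. Odds = p/(1 − p). Subgroup OR = community odds / control odds. Interaction OR = OR in non-compliers / OR in compliers.

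**Example A: children 40% of the sample, prevalence 5% (children) and 10% (adults), reluctance unrelated to risk.**

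Community arm:
- Non-compliers: (0.08 × 0.05 + 0.18 × 0.10)/0.26 = 0.0846, odds 0.0924.
- Compliers: (0.32 × 0.05 + 0.42 × 0.10)/0.74 = 0.0784, odds 0.0850.

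Control, adults coded non-compliers:
- Non-compliers: (0.08 × 0.05 + 0.60 × 0.10)/0.68 = 0.0941, odds 0.1039.
- Compliers: 0.05, odds 0.0526.
- Subgroup ORs 0.0924/0.1039 = 0.89 and 0.0850/0.0526 = 1.62; interaction OR 0.89/1.62 = **0.55**.

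Control, adults coded compliers:
- Non-compliers: 0.05, odds 0.0526.
- Compliers: (0.32 × 0.05 + 0.60 × 0.10)/0.92 = 0.0826, odds 0.0900.
- Subgroup ORs 1.76 and 0.94; interaction OR **1.86**.

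With the same people and no effect, the result changes direction with the coding alone.

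**Example B: children 40%, prevalence 10% at all ages, reluctant people at twice the odds.** Splitting each 10% gives 8.56% in willing and 15.77% in reluctant children, and 7.96% and 14.75% in adults. With control adults coded non-compliers, the subgroup ORs are 1.48 and 0.96 and the interaction OR is **1.55**. There is no age difference in prevalence here, so adjusting for age would not remove it.

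**Example C: as A, but reluctant people at twice the odds and control adults coded compliers.** Subgroup ORs 1.65 and 0.78; interaction OR **2.12**.

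**Range over all assumed combinations, true value 1.00:**

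| Treatment of control adults | Expected interaction OR |
|---|---|
| Coded non-compliers | 0.55 to 1.55 |
| Coded compliers | 1.00 to 2.12 |
| Left out of control only | 0.99 to 1.10 |
| Children only in both arms, identical compliance | 1.00 |

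In the third row the interaction is nearly right, but the two subgroup ORs behind it are not. In Example A they are 1.76 and 1.62 with no true effect.

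**The case against.** Three objections carry weight.

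First, a reader might infer that the test is biased by construction and must show heterogeneity even if deworming did nothing. The document does not support that. The school programme runs in all communities, and the volunteers treat household members who are not enrolled. As written, enrolled children therefore receive the same annual teacher-delivered offer in every arm. If their compliance is also the same across arms, the expected interaction OR is 1.00. It is also 1.00 if neither reluctance nor age is related to infection risk. This objection stands: the bias is possible and unsigned, not certain.

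Second, the analysis plan is not shown and the Data monitoring Committee is to approve it. It could restrict the subgroup to children, or define it from history with the national school programme or the earlier lymphatic filariasis rounds. That is possible, but the article states no such definition. It names the factor for formal testing without restriction, and a children-only version would drop the adults, whose treatment is a main difference between the arms. No definition built on compliance with trial treatment solves the problem across all ages.

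Third, the article says particular attention will be given to non-compliers in all study groups. That sentence is in the section on mathematical modelling and cost-effectiveness. It concerns transmission modelling, and it gives control adults no compliance status for a randomised comparison.

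**Conclusion.** The point holds in a limited form. The planned interaction test on frequent non-compliance is not protected by randomisation, and among adults the subgroup has no control counterpart. With no treatment effect, the expected interaction OR lies between about 0.55 and 2.12 in the cases examined. That range rests on assumed prevalences, age mix and risk in reluctant people, and on the choice of coding for control adults. It shows how far the result could move; it does not predict the result in this trial.

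A reader might also infer that the randomised comparison as a whole is compromised. It is not: the primary analysis remains by groups as randomised. The defect is confined to one of five listed secondary subgroup factors. It is worth correcting because the result would carry the standing of a prespecified formal test.

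**What to change.** Remove frequent non-compliance from the factors listed for formal interaction tests. Report results by compliance as description only, labelled non-randomised, with a statement of how control adults are handled. For the scientific question, rely on the work on persistent and irregular non-compliers already planned under Mathematical modelling and cost-effectiveness analysis.

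If a formal test is still wanted, use only a factor fixed before randomisation and measured identically in all arms. Because new people are drawn at each survey, the 30-month sample cannot be assumed to have an individual baseline record of compliance, so the availability of such a factor would need to be shown first.

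Do not substitute a complier-average causal effect with arm as instrument. That requires allocation to affect a person's infection only through that person's own treatment. The trial aims to reduce transmission, and the Randomisation section itself recognises lower exposure arising from reduced transmission elsewhere. Untreated people in treated clusters may therefore benefit, and the exclusion restriction fails.

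The cost is a change of one phrase and the loss of one formal secondary subgroup test. No new data are needed for the deletion.
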